### Clinical effectiveness

#### Primary analyses

The primary clinical analyses aim to examine whether the eHealth PPI has a significant clinical effect on positive mental health (i.e., MHC-SF), which will be evaluated in the RCT of study 2. The primary analysis will be an Analysis Of Covariance (ANCOVA), which aims to compare the three independent RCT conditions on positive mental health scores at the 12-month post-PPI measurement, with the pre-PPI measurement serving as a covariate.

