### Clinical effectiveness

#### Primary objective

Our primary clinical aim is to examine whether offering the eHealth PPI to various patients during the waiting period and their loved ones, followed by a mental health treatment for patients, is clinically effective in terms of improving positive mental health scores (primary outcome) at the 6-month and 12-month post-PPI measurement, compared to TAU. We hypothesize that introducing this eHealth PPI in condition 1 (PPI for patients only) and in condition 2 (PPI for patients and loved ones), followed by a mental health treatment, is clinically more effective, compared to condition 3 (TAU).

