#### A priori sample size

The a priori sample size in study 2 is based on the anticipated change in positive mental health between baseline and one-year treatment follow-up at the clinical setting in the intervention conditions compared to the control group. Compared to arm 3 (i.e., TAU), a medium effect size of Hedges’ g = 0.45 is assumed for both PPI arms followed by a mental health treatment (i.e., arms 1 and 2). The effect size of Hedges’ g = 0.45 is conservatively estimated based on prior studies about PPI effectiveness [21, 45], assuming an overlap in treatment mechanisms when combining a PPI with a subsequent mental health treatment. The Mental Health Continuum – Short Form (MHC-SF) is defined as the primary outcome [46], which is justified in the section on ‘’Data collection’’. Using a pretest-posttest design for this primary outcome, the required sample size was estimated at 207 patients, including 69 patients per treatment arm under a 5% Type I error rate, 80% statistical power, and an equal allocation ratio. While the PPI + mental health treatment arm including loved ones (arm 2) is expected to yield a larger effect size than the PPI + mental health treatment arm without loved ones (arm 1), the actual difference between both effect sizes is unknown due to the novelty of the inclusion of loved ones. In the absence of previous studies, we will conservatively assume identical effect sizes for both arm 1 and arm 2, which can be compared to arm 3 (TAU) with a sufficient degree of certainty. In addition, we still aim to compare arm 1 to arm 2 exploratively, knowing that these specific comparisons may not be adequately powered. Assuming a 35,5% attrition rate between baseline and the 1-year follow up measurement following treatment completion based on previous findings [47, 48], a total sample size of 207/(1–0.355) = 321 participants (*n* = 321) is required, yielding 107 patients per treatment arm. Since the second arm involves one loved one per patient, this arm will contain 214 participants. Thus, a total sample size of 428 participants will be required, including 321 patients and 107 loved ones.

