#### Interim analysis: sample size re-estimation

To re-assess the assumed effect size, the sample size and the dropout rate in study 2, incoming data will be monitored by an independent statistician, using an unblinded interim analysis [49]. The sample size reassessment will be conducted when a pre-specified fraction of the data from the originally intended sample are collected, while data collection is ongoing [49]. Although larger data fractions may provide more accurate insights in the expected effect sizes, the current RCT should perform interim analysis relatively early to prevent excessive inclusion of participants. Therefore, an early interim analysis will be performed when 35% of the anticipated complete cases are collected (i.e., when the 6-month post-intervention data of 0.35 * 207 = 72 complete *patient cases* are collected). For the same reason, data from a surrogate timepoint, namely six months following PPI-completion, will be used for interim analysis. While the information obtained may be limited, this selected data fraction is expected to produce relevant information to reassess the effect size estimate (and hence, the sample size) compared to a priori power analysis only [49]. Importantly, this 6-month post-PPI timepoint allows for timely sample size reassessment if the expected average inclusion rate of 5 participants per week is achieved. If the actual average inclusion rate substantially deviates from this assumed inclusion rate of 5 participants per week, a more timely cut-off point for sample size re-assessment will be determined.

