### Visual overview of data collection in both studies

The aforementioned questionnaires will be used at several points in time during study 1 and study 2. In both studies, the time spent on each measurement will be at most 30 min. An overview of all proposed measurements for patients and loved ones in both studies is presented in Tables 1 and 2.

**Table 1 Tab1:** All questionnaires for each measurement in study 1 (RSCD) among patients and loved ones

	T0:pre-PPI-measurement	T1: measure following module 1	T2: measure following module 2	T3: measure following module 3	T4: measure following module 4	T5: measure following module 5	T6: measure following module 6	T7: measure following module 7	T8: measure following module 8	T9: measure following module 9
MHC-SF	*x **				x *					x *
BSI	*x **									x *
SUS										*x **
Post-module process questions		*x **	*x **	*x **	*x **	*x **	*x **	*x **	*x **	*x **
Clinical profile	*x*									
Demographics	*x **									
Expectations	*x **									
PHQ-9	*x**									*x**
RSS	*x **									*x **
LOT-R	*x **								*x **	*x **
SCS-SF	*x **		*x **	*x **						*x **
SBI	*x **					*x **	*x **			*x **
GQ-6	*x **							*x **		*x **
BRS-NL	*x **									*x **

*x* = patient; ***= loved one; *MHC-SF* Mental Health Continuum – Short Form, *BSI* Brief Symptom Inventory,* SUS* System Usability Scale; Post-module process questions = questions related to the performance of each PPI module from a process evaluation perspective; Clinical profile = mental health complaints, symptomatic severity; Demographics = sex, age, income, education; Expectations = participant expectations regarding the eHealth PPI *PHQ-9* Patient Health Questionnaire – 9, *RSS* Relational Satisfaction Scale, *LOT-R* Life Orientation Test – Revised, *SCS-SF* Self-Compassion Scale – Short Form, *SBI* Savoring Beliefs Inventory, GQ-6 = Gratitude Questionnaire – 6; BRS-NL = Brief Resilience Scale – NL

**Table 2 Tab2:** All questionnaires for each measurement in study 2 (RCT) among patients and loved ones

	T0: Pre-PPI measurement	T1: Post-measure following immediate PPI completion	T2: 3-month measure following PPI completion	T3: 6-month measure following PPI completion	T4: 9 month measure following PPI completion	T5: 12-month measure following PPI completion	T6: 12-month measure following treatment completion
MHC-SF	*x **	*x **	*x*	*x*	*x*	*x*	*x*
BSI	*x **	*x **	*x*	*x*	*x*	*x*	*x*
SUS		*x **					
Post-module process questions		*x **					

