## Data analysis

All analyses of (cost-)effectiveness will be performed in accordance with the Intention-To-Treat (ITT) principles, meaning that data from all participants will be analysed according to the study condition to which they were initially assigned, regardless of adherence [94]. Assessment of baseline inequalities between study conditions will be performed and followed up, if needed. Due to the longitudinal nature of study 1 and study 2, dropout and other processes causing missing data are expected [95]. Appropriate missing data handling techniques will be applied after assessment of the magnitude, mechanisms, and patterns of missing data [96]. A one-sided alfa of 0.05 will be applied in both studies. Since multiple comparisons between RCT arms will be performed in study 2, this significance level of 0.05 will be adjusted to manage Type I error probability, using the Holm-Bonferroni method [97].

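### The primary time point is stated in three conflicting ways, so the stated 80% power belongs to a visit that the primary test does not use

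*Protocol article*

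**What the plan says.** Three sections of the protocol article fix when the primary outcome is judged.

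- **Objectives, Clinical effectiveness, Primary objective:** the aim concerns "positive mental health scores (primary outcome) at the 6-month and 12-month post-PPI measurement, compared to TAU". In Table 2 these are visits T3 and T5.
- **Data analysis, Clinical effectiveness, Primary analyses:** one ANCOVA is to "compare the three independent RCT conditions on positive mental health scores at the 12-month post-PPI measurement, with the pre-PPI measurement serving as a covariate". This is T5 alone.
- **A priori sample size:** the calculation is "based on the anticipated change in positive mental health between baseline and one-year treatment follow-up at the clinical setting", in the intervention arms against control. The effect size there, "g = 0.45 is assumed for both PPI arms followed by a mental health treatment", is for the PPI and the later treatment together, and the 35.5% attrition also runs to one year after treatment completion.

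Table 2 lists that last visit in its own column, "T6: 12-month measure following treatment completion", next to T5, which is timed from completion of the PPI.

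On multiplicity, the Data analysis section sets a one-sided alpha of 0.05 and continues: "Since multiple comparisons between RCT arms will be performed in study 2, this significance level of 0.05 will be adjusted", by Holm-Bonferroni. It gives no rule for time points.

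**The concern.** T5 and T6 are timed from different events: T5 from the end of the PPI, T6 from the end of the later treatment. The note to Fig. 1 expects most patients to start that treatment more than five weeks after the first post-measurement. Neither the effect nor the attrition assumed for T6 can simply be carried to T5, and the article offers no argument for doing so.

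Two things are at stake. The 80% power is a statement about T6, while the trial will be judged by a test at T5. And if the result is positive at 6 months but not at 12, or at T6 but not at T5, the text lets the trial be called a success or a failure. A later analysis plan can agree with at most one of the three statements, so this is not a detail left for it to fill in.

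The interim analysis makes the point more pressing. It is meant to reassess effect size and dropout and, if needed, replace the sample size, which requires one agreed target endpoint.

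**Working it through.** **1. The plan's own figures.** Inputs from A priori sample size: g = 0.45, 5% type I error (sidedness not given there), 80% power, 69 complete patients per arm (207 in total), 35.5% attrition.

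- Attrition step: 207 / (1 − 0.355) = 320.9, so 321; 69 / 0.645 = 107 per arm. This reproduces, so the recruitment target was built for attrition to T6.
- Base step, without gain from baseline: n per arm = 2 × ((z for alpha + z for power) / g)².
  - One-sided 0.05: 2 × ((1.645 + 0.842) / 0.45)² = 61.1, so 62.
  - One-sided 0.025 (first Holm step with two contrasts) or two-sided 0.05: 2 × ((1.960 + 0.842) / 0.45)² = 77.5, so 78.

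Neither gives 69. The text refers to a pretest-posttest design, so a baseline correlation r was probably used but is not stated. With ANCOVA at one-sided 0.025, 1 − r² = 69 / 77.5 = 0.890, so r = 0.33. With a change score, 2(1 − r) = 0.890 gives r = 0.55. The figure of 69 is thus not reproducible from the stated inputs, but it is not shown to be wrong. I use r = 0.33 below because it returns the plan's own 69 per arm for an ANCOVA.

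**2. Power at T5 with the planned 107 per arm.** Attrition to T5 is not given, so it is an assumption, shown as a range. Power = Φ(g × √(n/2) / √(1 − r²) − 1.960), with n = 107 × (1 − attrition).

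Check at 35.5%: n = 69.0, and 0.45 × √34.5 / √0.890 − 1.960 = 0.842, which is 80% power.

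| Assumed attrition to T5 | n per arm | Power if g = 0.45 |
|---|---|---|
| 15% | 91.0 | 90% |
| 20% | 85.6 | 88% |
| 25% | 80.2 | 86% |
| 30% | 74.9 | 83% |
| 35.5% | 69.0 | 80% |

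If the effect at T5 is smaller than the one assumed for T6, power at 35.5% attrition is 70% (g = 0.40), 59% (g = 0.35) or 46% (g = 0.30).

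**3. Family-wise error.** Two contrasts, each PPI arm against a shared TAU arm, are simulated under the null with equal arms. Each is tested at one-sided 0.025, the first Holm step. The correlation between time points is not in the article and is assumed.

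| Success rule | Correlation 0.5 | Correlation 0.7 | Correlation 0.8 |
|---|---|---|---|
| One time point, fixed in advance | 4.5% | 4.5% | 4.5% |
| Success at either 6 or 12 months | 8.1% | 7.4% | 7.0% |
| Same contrast at both 6 and 12 months | 0.9% | 1.5% | 2.0% |

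The middle row exceeds 5% because Holm, as stated, covers comparisons between arms and not time points.

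**The case against.** The best defence is that the analysis section is clear: it specifies one primary test at one visit. The other visits are covered by the multilevel model across the seven measurements, under Secondary analyses. The objective joins 6 and 12 months with an and, not an or. Attrition to T5 is likely no higher than to T6, so 321 patients may even be generous. This stands as far as consequences go: neither an inflated error rate nor a loss of power follows from the text alone. It does not remove the conflict, because the objective still gives a second primary visit and the sample size a third.

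A reader might infer more than the article supports, in four ways.

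- *That the error rate depends on which time point is used.* It does not. Each one, fixed in advance, gives about 4.5%. Inflation needs an either-visit rule or a choice made after seeing data.
- *That the primary test is a non-directional three-group F test at odds with the one-sided alpha.* The article names an ANCOVA comparing three conditions but no omnibus test. The directional hypotheses and the Holm adjustment of arm comparisons point to pairwise contrasts.
- *That arm 1 against arm 2 takes part of the Holm family and so costs power.* Nothing says it does. Objectives, A priori sample size and Discussion all treat that comparison as exploratory.
- *That the interim adds a fourth conflicting time point.* It does not. The article says openly that "data from a surrogate timepoint, namely six months following PPI-completion, will be used for interim analysis".

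**Conclusion.** Wrong as written. The objective, the primary analysis and the sample size name different primary time points, and the conflict rests on the current text without any assumption. The stated 80% power and 35.5% attrition belong to T6, which is not the planned primary test, and a split result across visits has no predefined reading.

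The size of the effect on power is open. At T5 it is 80–90% for attrition of 35.5–15% if g = 0.45 holds there, and 46–70% at 35.5% attrition if g is 0.30–0.40. All of these figures assume a baseline correlation of 0.33 and one-sided 0.025 per contrast. Family-wise error of about 7–8% applies only to an either-visit rule, with assumed correlations of 0.8–0.5 between the visits.

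**What to change.** Before the interim analysis:

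1. Name one primary time point and use it in Primary objective, A priori sample size and Primary analyses. T5 is the natural choice because the analysis section already specifies it. Make the 6-month visit and T6 secondary.
2. In A priori sample size, give the basis of the effect size, the attrition and the assumed baseline correlation for that visit. Keep the planned number of patients and report the power that it gives.
3. In passing, state that the primary tests are the two directional ANCOVA contrasts, each PPI arm against TAU, with Holm over these two. This agrees with arm 1 against arm 2 being exploratory.

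The cost is a change of wording in three sections, one sentence on the contrasts and a fresh power statement. The registry record is not at hand, so whether it also needs an update cannot be judged here. The downside is that the restated power may be less favourable than 80% if the effect that can be justified at T5 is below 0.45.

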#### Secondary analyses

The secondary clinical analyses of study 2 aim to evaluate whether the eHealth PPI significantly affects other outcome measures, in addition to examining the effects of including loved ones in the eHealth PPI. Outcome scores on the other positive psychology constructs (i.e., SCS-SF, SBI, LOT-R, GQ-6, and BRS-NL), physical and psychological symptoms (i.e., BSI), depression (i.e., PHQ-9), and relational satisfaction (i.e., RSS) will be addressed in both studies. In study 2, an ANCOVA will be used again, employing the pre-PPI-measurement as a covariate. Using this method, a comparison will be made between the pre-PPI measurement and the immediate post-PPI measurement to analyse the scores on the SCS-SF, SBI, LOT-R, GQ-6, BRS-NL, BSI, PHQ-9, and RSS across the three independent RCT conditions. Using this approach, the effects of including loved ones in the second condition *(eHealth PPI for patients and loved ones)* will also be examined, relative to the other conditions. An additional visual analysis — considered foundational for single-case designs [98] — will be employed in study 1 to identify preliminary effects within individuals for descriptive purposes without aiming to establish clinical effectiveness or to guide study adjustments.

In study 2, multilevel regression modelling will be used to examine and compare the average longitudinal trajectory of change on the primary outcome (i.e., MHC-SF) across the three RCT arms. Based on theoretical considerations, certain demographics (i.e., education and literacy, employment status, sex, and age) and clinical profiles (i.e., severity of psychological complaints, and diagnosis) are considered relevant group-level moderators for modelling such change trajectories. Using these moderators in a multilevel regression model, moderation analyses will be employed to examine variations in longitudinal change trajectories between the RCT conditions on the primary outcome (i.e., MHC-SF) and relevant secondary outcomes (i.e., BSI, MHQoL, and BRS-NL) across the seven RCT measurement points. Using the same moderation analyses, the average trajectory of change for certain subpopulations will be examined across the seven RCT measurement points to evaluate how different subpopulations respond to the eHealth PPI over time. Notably, moderation analyses for subpopulations may reveal different associations between group-level moderators and PPI effectiveness, even if these associations cancel each other out in the overall change comparisons between the three RCT conditions [99].

### Economic evaluation

#### Valuation of clinical outcomes

In the CEA of study 2, clinical outcomes derived from the MHC-SF, BSI and BRS-NL will be valued, using specific conversion guidelines [65, 66]. In the CUA of study 2, utility scores derived from the EQ-5D-5 L, MHQoL and ICECAP-A will be converted to QALYs using existing methods, including the area-under-the-curve method [100]. While the EQ-5D-5 L scores will serve as the main quality of life outcomes, the MHQoL and ICECAP-A scores will be used in a sensitivity analysis. In general, MHQoL and ICE-CAP-A scores are expected to reflect wellbeing differently in patients facing psychological complaint, when compared to EQ-5D-5 L scores [81].

#### Valuation of societal costs

The sum of healthcare costs, productivity losses, and intervention costs will be estimated for the eHealth PPI conditions (arm 1 and arm 2) and the TAU condition (arm 3), yielding the societal cost per RCT arm. Firstly, the reported consumption of each health service type and medication in the TIC-P will be multiplied by a respective reference price, using the guidelines for economic evaluation issued by ZIN [65, 66]. Secondly, productivity losses due to absenteeism and presenteeism, as measured by the TIC-P, will also be addressed. Absenteeism will be valued using the friction cost method [100]. Using this method, the reported hours of absence will be multiplied by the average hourly rate of a working individual in The Netherlands, to a maximum of 12 weeks. After 12 weeks, initial productivity losses due to absenteeism are assumed to be restored. Presenteeism will be derived from the additional hours that participants need to finish their work due to health complaints. Likewise, these additional hours are multiplied by the average hourly rate of a working individual in The Netherlands.

Within the eHealth PPI, [1] personnel time will be valued using standard reference prices per hour, based on the staff’s professional category (e.g., psychologist, student psychologist, and IT support). Additional [2] training costs, as measured by resources and preparation time, will be valued. Depending on training prices and the total number of required trainings during the RCT, this cost component will be calculated by multiplying both. In addition, [3] licensing and maintenance costs, [4] development costs, and [5] technical support costs will be monetized, using invoices provided by the eHealth organization. If invoices are issued on a per-user basis, the unit price per participant can be applied directly. However, if invoices are issued as an annual organizational fee, the average annual cost per user will be calculated by dividing the total annual fee by the annual number of eHealth PPI participants (within the billing period).

In the second RCT arm, both patients and their loved ones will have an individual user account to engage with the eHealth PPI. Hence, total intervention costs of this eHealth PPI condition (arm 2) are expected to outweigh those of the patient-only eHealth PPI condition (arm 1). All healthcare, non-healthcare and intervention cost components will be indexed to the most recent base year, using the latest costing manual in Dutch healthcare [66]. If necessary, all estimated costs will be extrapolated to an extended time horizon that is not covered by the 3-month recall period. Following the ITT-principles throughout the entire RCT duration, the total sum of healthcare costs, non-healthcare costs, and intervention costs will be calculated and averaged per participant within each RCT condition, yielding an estimate of the average societal cost per RCT condition. These estimates will then allow for comparative base-case analyses of cost-effectiveness.

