**Fig. 1 Fig1:**
[figure not shown]
Flowchart of the proposed RCT (study 2). Note: *Predicted start of the official intake and a mental health treatment for most patients: Although the official intake and treatment could take place in principle after the pre-measurement, most patients will likely receive treatment more than 5 weeks after completion of the first post-measurement due to long waiting times in Dutch mental healthcare (i.e., > 14 weeks)

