#### Measuring societal costs for the CEA and CUA

In both the CEA and CUA, costs will be measured among patients from a societal perspective, including healthcare costs (i.e., health services use and medications), productivity losses (i.e., absenteeism and presenteeism), and intervention costs (i.e., the costs of implementing the intervention). To measure healthcare costs and productivity losses, a 3-month recall period will be used. Consumption of health services, medications, and productivity losses in patients facing psychological complaints will be measured, using the Treatment Inventory of Costs in Patients with psychiatric disorders (TIC-P) [87].

By definition, the TIC-P was developed as a generic questionnaire to estimate societal costs across all Dutch adult mental health populations within inpatient and outpatient clinical settings. Using both categorical multiple choice and numerical open ended questions, the TIC-P aims to measure 3 subscales: general demographics (7 items), healthcare consumption (38 items), and productivity losses in both the formal and informal workspace (12 items) [87]. In the absence of subscale estimates (e.g., Cronbach’s alpha) on reliability, Cohen’s Kappa was still considered highly satisfactory for most separate items on healthcare consumption, and satisfactory for most items on productivity losses [88]. Productivity losses in the workspace are based on absenteeism (i.e., not being able to work) and presenteeism (i.e., reduced productivity in the workspace). Informal productivity losses related to unpaid work will also be measured. Patients will report their hours of absence (i.e., absenteeism) and the additional hours they needed to finish work due to health complaints (i.e., presenteeism).

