
Over the next 4 years, interim (cost-)effectiveness analyses will be performed to carefully monitor the preliminary results, while data collection is still ongoing. Definitive conclusions regarding (cost-)effectiveness will be drawn when the data collection is fully completed, which is expected to take 5–6 years. In addition to supporting loved ones, the proposed eHealth PPI may support the patient’s mental health relatively early during the waiting period, potentially reducing the total number of subsequent mental health treatment sessions required for clinical remission. In that case, the proposed eHealth PPI might indirectly improve the availability of mental health professionals, thereby reducing the long-term burden of waiting lists in mental healthcare and potentially making it a (cost-)effective intervention. Addressing the proposed research gaps may enhance our academic understanding of transdiagnostic eHealth PPIs, including their clinical and financial implications. Hence, upcoming study results may be used to inform resource allocation decisions regarding the implementation of eHealth PPIs within Dutch mental healthcare and potentially beyond.

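### Index treatment given after T5 falls in no TIC-P recall window, and an extrapolation with no stated wave or rate stands in for it

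*Protocol article*

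**What the plan says.** **Source and recall.** The section on measuring societal costs states: "To measure healthcare costs and productivity losses, a 3-month recall period will be used". The TIC-P is the only instrument named there for health services, medication and productivity losses. The valuation section multiplies the consumption reported in it by reference prices.

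**Schedule.** Table 2 gives the TIC-P to patients at all seven measurements. T1 to T5 run from the end of the intervention in three-month steps to "T5: 12-month measure following PPI completion". The last column is "T6: 12-month measure following treatment completion", so its calendar time differs by patient. No TIC-P is placed between the two.

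**Start of treatment.** The note to Fig. 1 expects that "most patients will likely receive treatment more than 5 weeks after completion of the first post-measurement".

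**Costing.** The valuation section says that, if necessary, "all estimated costs will be extrapolated to an extended time horizon that is not covered by the 3-month recall period". It then totals costs across the full length of the trial. The base-case section discounts costs that fall beyond one year.

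**Mechanism.** The Discussion describes the intervention as "potentially reducing the total number of subsequent mental health treatment sessions required for clinical remission".

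**The concern.** The T6 recall window opens nine months after treatment has ended, so it cannot contain any of the index treatment. The T5 window closes 12 months after the intervention. Sessions between T5 and the end of treatment are therefore reported at no visit. The stated costing horizon includes that stretch of time, and the only remedy given is a conditional extrapolation that names neither a source wave nor a rate.

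Societal cost-effectiveness is the primary economic objective, and fewer treatment sessions is the route to savings that the Discussion names. For patients treated beyond T5, the data that would show such a saving are partly not collected. An analysis plan written later can choose how to fill the gap, but it cannot recover sessions that nobody recorded.

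**Working it through.** The plan gives no figure of its own to reproduce on this point, so the check is arithmetic on the recall windows.

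**Inputs from the article**
- Intervention period of 8 weeks. Counting from T0, T1 is at week 8.
- T2 to T5 follow at 3-month (13-week) steps: weeks 21, 34, 47 and 60.
- TIC-P recall is 3 months (13 weeks).
- T6 is 52 weeks after treatment completion.

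**Inputs assumed**
- Wait *W* from T0 to the start of treatment: 14 weeks, the Dutch norm cited in the Background. This fits the Fig. 1 note, since 8 + 5 = 13. A wait of 26 weeks serves as a second value.
- Treatment length *D*: 26, 52 or 78 weeks, continuous. The documents give none.
- Weekly cost after treatment as a fraction *k* of weekly cost during treatment: 0.2 to 0.5. The documents give none.

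**Coverage up to T5.** Each window from T2 to T5 begins where the previous one ends, so recall is unbroken to week 60.

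**Coverage after T5**
- T6 = W + D + 52, and the T6 window opens at W + D + 39. Treatment ended at W + D, so the window holds 0 weeks of index treatment for every W and D.
- Time from T5 to T6: W + D + 52 − 60 = W + D − 8.
- Unobserved time: W + D − 8 − 13 = W + D − 21.
- Unobserved treatment: max(0, W + D − 60).

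| W | D | T5 to T6 | Unobserved | Treatment weeks unobserved |
|---|---|---|---|---|
| 14 | 26 | 32 | 19 | 0 |
| 14 | 52 | 58 | 45 | 6 (6/52 = 12%) |
| 14 | 78 | 84 | 71 | 32 (32/78 = 41%) |
| 26 | 26 | 44 | 31 | 0 |
| 26 | 52 | 70 | 57 | 18 (18/52 = 35%) |
| 26 | 78 | 96 | 83 | 44 (44/78 = 56%) |

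Treatment is missed only if D > 60 − W: more than 46 weeks at W = 14, or more than 34 weeks at W = 26.

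**What each way of filling the gap does (W = 14).** The unit is one week of in-treatment cost. True cost from T5 to T6 is the unobserved treatment weeks plus *k* times the 52 weeks after treatment.
- *D = 52.* True cost is 6 + 52k, which is 16.4 at k = 0.2 and 32 at k = 0.5. Carrying the T6 rate back gives 58k, or 11.6 and 29: 29% and 9% too low. Carrying the T5 rate forward over the 45 unobserved weeks gives 45 + 13k, or 47.6 and 51.5: 190% and 61% too high.
- *D = 78.* True cost is 32 + 52k, which is 42.4 and 58. The T6 rate gives 84k, or 16.8 and 42: 60% and 28% too low. The T5 rate gives 71 + 13k, or 73.6 and 77.5: 74% and 34% too high.
- *D = 26.* Treatment ends at week 40, before the T5 window opens at week 47. Both rates are then post-treatment rates, and neither choice makes an error in this model.

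**Effect on a saving.** Suppose TAU patients need 78 weeks and intervention patients 66, both with W = 14. The true difference is 12 treatment weeks. Carrying T6 back records 84k − 72k = 12k, which is 2.4 to 6 weeks, or 20% to 50% of the saving. Carrying T5 forward records (71 + 13k) − (59 + 13k) = 12 weeks: the full difference, but with both arms' costs too high.

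**The case against.** **The extrapolation is conditional and open.** It applies only if necessary, and no wave or rate is given. A reader might infer that treatment after T5 will be costed at a treatment-free rate, that any saving will be recorded as zero, and that the result is biased against the intervention. The documents support none of these. The first holds only if the T6 rate is carried back. Even then the saving is attenuated to 20% to 50% in the example above, not erased. Carrying T5 forward errs in the opposite direction on cost levels. This part of the objection stands.

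**Part of any saving is seen.** Sessions saved before T5, through lower frequency or an earlier end, are captured at T2 to T5. This also stands. Only the part falling after T5 is lost.

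**Size and reach are unknown.** Treatment length and the post-treatment cost fraction are assumed, the percentages concern T5-to-T6 cost only, and the share of patients treated past T5 is not known. This stands. No effect on the ICER is shown.

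**The horizon is not fixed outright.** The primary clinical analysis is at 12 months post-intervention, where recall is complete, and no sentence names T6 as the base-case horizon. However, costs are totalled over the whole trial, later costs are discounted and the TIC-P is repeated at T6, so the text as written includes the gap.

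**An article condenses.** The extrapolation method may well sit in a fuller document. The visit schedule, recall length and data source are stated here, and they create the gap whatever method is chosen. The planned sensitivity analyses on costs and service use are generic. They can vary a guess but cannot supply the missing sessions.

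**Conclusion.** The point holds as a gap in ascertainment. TIC-P recall is continuous only to T5, and the T6 window can never contain the index treatment. For any patient still in treatment at T5, the remaining sessions are recorded nowhere that the article names, although their cost belongs to the stated total. The direction of the resulting error is undetermined because the filling rule is unspecified.

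The size depends on treatment length, which the documents do not give. With a 14-week wait from baseline and continuous treatment, nothing is missed at 26 weeks, a modest part at 52 weeks and about two fifths at 78 weeks. A longer wait raises these shares. If treatment ends by T5, no index treatment is lost, though some post-treatment time stays unobserved.

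**What to change.** Obtain the dates and counts of treatment sessions after T5 from the participating clinic's records, and cost them at the reference prices already planned. All patients are recruited from this one clinic. T6 cannot be scheduled without a treatment completion date, although the article does not say where that date comes from. Add matching wording to the consent form, which is easiest at enrolment.

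Reword the extrapolation sentence in the valuation section so that it covers only the remaining TIC-P cost categories, names the wave and rate used, and is reported as a labelled scenario.

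If records cannot be obtained, present the fully covered period to T5 as the base case and the longer horizon as a scenario.

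The cost is some data-linkage work with one clinic, a consent addition and a revised costing sentence. Care obtained elsewhere during the gap would stay uncertain.
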